### Study design

This study protocol has been written according to the SPIRIT statement (Standard Protocol Items for Randomized Trials) [44].

The i-BEAT project includes a multimethod three study arms approach. Study 1 encompasses a cross sectional and a longitudinal questionnaire-based survey. At baseline and one year later, questionnaire-based data is acquired online and the sample is screened to identify youth with LOC and HCG. The procedure is based on our pilot study BEAT (Binge Eating for Adolescent Treatment; DRKS00014580). App based daily-life data is assessed in a subgroup with LOC and in a HCG. We compare changes concerning the primary and secondary end points of study 1 between LOC versus HCG at T1.0, after one year at T1.6 and repeatedly during the 7-days of the App based daily life study (T1.5). Study 2 applies an adapted VR Cyberball task in the laboratory [45] and primary and secondary outcomes are compared between youth with LOC and age and gender matched HCG youth. Study 3 is a randomized wait-list between and within-subject online intervention study with a repeated measures design to evaluate the separate and additive effect of each of the two 6-weeks CBT-E or INTER-E modules (within subject effect) up to 6 and 12-months follow-up. After completion of the first module, participants wait 3 weeks until they receive the other module. We compare changes concerning the primary and secondary end points in participants from T3.00 to T3.1, T3.1 to T3.2 (active treatment in module 1), T3.2 to T3.3 (three weeks waiting between modules) and T3.3 to T3.4 (active treatment in module 2) as well as from T3.4 to the follow ups T3.4 and T3.5 (see Fig. 2 for study procedure).

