Hypotheses concerning (1) primary and (2) secondary outcomes in study 3:Applying an INTER-E or a CBT-E module leads to a greater reduction of the number and severity of LOC episodes, problems of emotion regulation and negative mood than a 4-weeks’ waiting period.The INTER-E module reduces weekly RS experiences, negative mood and problems of emotion regulation more strongly than the CBT-E module, whereas CBT-E decreases numbers and severity of weekly LOC episodes and urge to engage in disinhibited eating more importantly than the INTER-E module.Applying the additional CBT-E or INTER-E module results in additional improvement of RS experiences, numbers or severity of weekly LOC episodes, problems of emotion regulation and urge to engage in disinhibited eating.BMI remains stable during active treatment and follow-up.Effects of the initial INTER-E or the CBT-E module remain stable during a 3-weeks pause.Effects of the treatment remain stable during 6- and 12-months follow-up.Therapist ratings of improvement are in line with the self-report of the patients.CBT-E and INTER-E result in similar acceptance, usability, attrition and adherence rates.

We further aim to explore epigenetic underpinnings (DNA methylation, DNAm) of RS and emotion regulation capacity [37]. DNAm patterns are thought to reflect exposure to various psychosocial influences across the life-span and have been shown to relate to behavioral, emotional and cognitive styles especially in youth [38, 39]. We seek to explore the DNAm levels of genes involved in stress regulation and social interaction (FK-506-binding protein 5 (FKBP5) [40], the glucocorticoid receptor (NR3C1) [41], oxytocin receptor (OXTR) [42, 43] and the serotonin transporter (SLC6A4) in youth with LOC compared to a HCG (prior to treatment) and in LOC prior versus post treatment.

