### Participants

Study 1 serves as a tool to increase awareness and recruit youth suffering from LOC and a HCG participating in all substudies. Youth with LOC participating in study 3 are randomized according to a permuted block design [46] to CBT-E or INTER-E first. Participants’ inclusion criteria for studies 1–3 are age between 14 and 24 years, sufficient German language competences and written informed consent. Criteria for LOC [47] are fulfilled and youth included if they experience at least 3 episodes of LOC during the last 3 months accompanied by at least 3 out of 5 behavioral indicators and/or some degree of distress, absence of AN or BN. Inclusion criteria for youth participating in the HCG are healthy body weight (BMI 18.5–24.9), absence of any past or present ED and absence of any present mental disorder according to the diagnostic interview. Youth from the LOC group are excluded if they suffer from any current mental disorder preventing safe participation in the i-BEAT study or if there is an intake of weight affecting drugs, participation in an ED related psychotherapy or weight loss treatment. Females in pregnancy or lactation are excluded. Additional in- and exclusion criteria for study 2 are intact or corrected vision capacity and nausea in VR. Figure 3 illustrates the study sample.

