### Data analysis

Data will be analyzed with the Statistical Package of Social Sciences (SPSS) and R. We will apply multiple regression models including covariates and testing specific predictors (study 1), multilevel models including moderators (App based study 1), between subjects analysis of covariance including moderators (study 2) and mixed between and within subjects analysis of covariance or linear mixed models (study 3). Exploratory epigenetic goals involve predictors and within-subject effects. Expected dropouts are assumed to amount up to 10–18%. Random occurrence should lead to equal distribution of dropouts in the different groups (LOC vs. HCG; CBT-E first vs. INTER-E first). However, in the case of an unequal distribution of the number of participants to the different groups, this issue will be addressed with multi-level models. Multi-level models are assumed to be robust against violations of equal group sizes [55]. Additionally, we will test whether a missing at random pattern is a reasonable assumption with respect to dropout.

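### Study 3 is labelled a randomised wait-list study, but only module order is randomised, and the module-versus-waiting hypothesis compares 6 weeks with 4 weeks in a fixed order, so time alone can create a difference in either direction

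*Protocol article*

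**What the plan says.** **Label.** Protocol article, Study design: "Study 3 is a randomized wait-list between and within-subject online intervention study".

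**Allocation.** Protocol article, Participants: "Youth with LOC participating in study 3 are randomized according to a permuted block design [46] to CBT-E or INTER-E first". The Data analysis section names the same two groups, "CBT-E first vs. INTER-E first", and no waiting group.

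**Hypothesis.** In Study aims and hypotheses, the first hypothesis for study 3 (H1 here) expects either module to reduce LOC episodes, "problems of emotion regulation and negative mood than a 4-weeks’ waiting period".

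**Intervals.** Study design gives the module length as "each of the two 6-weeks CBT-E or INTER-E modules (within subject effect") and then lists the periods: "We compare changes concerning the primary and secondary end points in participants from T3.00 to T3.1, T3.1 to T3.2 (active treatment in module 1"). A three-week wait between modules and the second module follow. The text does not name T3.00 to T3.1 as the 4-week wait. That is an inference from H1, from the order of the periods, and from the fact that the only other wait lasts three weeks.

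**The concern.** A randomised wait-list trial allocates some people to start and others to wait, and compares them over the same calendar interval. Natural course, regression to the mean and repeated measurement then act equally on both groups. Here both randomised groups receive an active module, and everyone appears to wait first. The wait is a baseline period, so H1 is a before-and-after comparison within people.

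Two problems follow. The wait always comes first, so any effect of period is confounded with treatment. The two intervals also differ in length by half, so total change over one is not comparable with total change over the other even if the untreated course is a straight line. H1 is the only study 3 hypothesis that compares a module with no treatment. The label invites readers to give it the weight of a randomised comparison.

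**Working it through.** **1. The plan's own figure.** The Sample size section gives N = 34 for f = 0.25, r = 0.5 and power 0.80 (the 0.05 is printed as β and read here as alpha). For a repeated-measures F test with m = 2 measurements, λ = f²·N·m/(1 − r) = 0.0625 × 34 × 2 / 0.5 = 8.5. Power is 0.808 with one group and 0.807 with two, and 34 is the smallest N that reaches 0.80. The figure reproduces, so sample size is not the fault.

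**2. Steady untreated change.** Let improvement be b SD per week with no treatment effect.
- Wait: 4b. Module 1: 6b. Ratio 6/4 = 1.5.
- Spurious difference in change: 6b − 4b = 2b.

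**3. Size of the error.** The H1 contrast is (Y2 − Y1) − (Y1 − Y0) = Y2 − 2Y1 + Y0, with Y0, Y1, Y2 at T3.00, T3.1, T3.2. With equal variances and a common correlation r, its variance is (6 − 6r) SD². At r = 0.5, the value in Sample size, this is 3 SD². Data analysis allows up to 18% dropout, so 120 × 0.82 ≈ 98 completers and SE = √3/√98 = 0.175 SD.

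The drift b is an assumption; the document gives none. Two-sided rejection at nominal 5%:

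| b (SD per week) | 2b | 2b/SE | False-positive rate |
|---|---|---|---|
| 0.025 | 0.05 | 0.29 | 5.9% |
| 0.05 | 0.10 | 0.57 | 8.8% |
| 0.10 | 0.20 | 1.14 | 20.8% |

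If r were 0.7, which is not in the document, SE would be √1.8/√98 = 0.136 and the last two rows would be 11.4% and 31.4%.

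**4. Untreated change that slows down.** Let symptoms decay exponentially at rate k, with the wait in weeks 0–4 and module 1 in weeks 4–10. The ratio of untreated change, module to wait, is e^(−4k)(1 − e^(−6k))/(1 − e^(−4k)). Half-lives are assumed:

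| Half-life (weeks) | Total change, module/wait | Per week: wait, module |
|---|---|---|
| 52 | 1.40 | 0.0130, 0.0121 |
| 26 | 1.31 | 0.0253, 0.0221 |
| 12 | 1.13 | 0.0516, 0.0387 |
| 8 | 0.98 | 0.0732, 0.0478 |
| 4 | 0.65 | 0.1250, 0.0539 |
| 2 | 0.29 | 0.1875, 0.0365 |

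The ratio crosses 1 at a half-life of about 8.4 weeks. Below that, total change favours the wait.

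**5. What equal time achieves.** The per-week contrast (Y2 − Y1)/6 − (Y1 − Y0)/4 has expectation b − b = 0 under a linear trend, so the duration mismatch disappears. Under any decelerating course in the table, the per-week change is larger in the wait, so a period effect remains and runs against the modules.

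**The case against.** A reader might infer that the design has a built-in bias towards the modules. The documents do not support that. It holds for steady or slow untreated improvement, but the Participants section selects on at least three LOC episodes in the preceding three months. Selection on recent symptoms invites regression to the mean, which would fall mainly in the wait and work against the modules. The direction is open.

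The drift can also be challenged. Over the ten weeks of wait plus module, 0.05 to 0.10 SD per week amounts to 0.5 to 1.0 SD of untreated improvement. The Epidemiology section cites longitudinal work suggesting that LOC is fairly persistent over years. With half the lower drift, the false-positive rate is about 6%. The 9–21% range is therefore an illustration and not an estimate.

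The article is also open about what is randomised, calls the design partly within-subject, and allows linear mixed models, which could scale for time. A fuller analysis plan may do so. That H1 will be reported as a randomised result is a prediction, not something the article says. Figures 2 and 3 could not be seen.

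What remains does not depend on those points. The label claims a property that the allocation sentence does not provide, and two sections agree on two sequence groups only. No analysis plan can turn the waiting period into a randomised comparator, and the stated interval lengths differ.

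**Conclusion.** The point holds in this form: by the text, study 3 is randomised to module order, and H1 is a non-randomised, fixed-order, within-person contrast of a 6-week interval with a 4-week one. Time alone can produce a difference. Under steady untreated improvement the factor is 1.5 in favour of the module, with a false-positive rate of about 9–21% at an assumed drift of 0.05–0.10 SD per week, r = 0.5 and 98 completers, and close to 5% at smaller drift. Under early improvement (half-life below about 8.4 weeks in the exponential illustration) or regression to the mean, the bias reverses and H1 could wrongly fail.

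This rests on reading T3.00 to T3.1 as the wait. The CBT-E versus INTER-E comparison at T3.2 is randomised and unaffected.

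**What to change.** 1. **Label.** Describe study 3 as randomised to module order with a non-randomised within-person waiting period, name T3.00 to T3.1 as that period, and reserve randomised inference for CBT-E versus INTER-E in module 1.
2. **Analysis of H1.** Estimate change per week in a piecewise mixed model using T3.00, T3.1 and T3.2, adding weekly module data where collected. As a sensitivity analysis, compare T3.00 to T3.1 with T3.1 to week 4 of the module. This should stay a sensitivity analysis: it leaves out the last two sessions, and it works only for outcomes measured weekly. Diagnostic assessment lists LOC episodes and emotion regulation or RS among the weekly measures, but not negative mood, and does not say that the weekly questionnaires run during the wait.
3. **Limits.** State that scaling by time removes the duration mismatch under a linear trend but not the period effect or regression to the mean, and report H1 as non-randomised evidence.

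The cost is wording and analysis specification, with no new participants or visits. The price is a slightly smaller apparent effect and a more modest claim for H1.

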**Fig. 2 Fig2:**
[figure not shown]

[figure not shown]
Instruments. *Note.* (1) The complete DIPS will be conducted after the questionnaire-based screening study 1 and before further participation in either the laboratory study 2 or the online treatment study 3. The DIPS will only be conducted, if participants indicated their interest in either study 2 or study 3. (2) The Weekly Binges Post-Interview (WBQ-Post-Interview) is performed at the measurement point "Post Module 2", see above. (3) The DIPS short version will be conducted again at measurement point "Post Module 2". This short version only checks for disorders that have been identified as prominent in the first DIPS, and does not ask for eating disorder pathology. Note, almost all questionnaires and scales that will be used in i-BEAT study have been validated in German in the past. The respective citations are presented in the list of abbreviations. Only few questionnaires have been developed for the project at hand and are marked as “self-developed”. For a more detailed overview of the instruments, see additional file 1, "Instruments"

### Participants

Study 1 serves as a tool to increase awareness and recruit youth suffering from LOC and a HCG participating in all substudies. Youth with LOC participating in study 3 are randomized according to a permuted block design [46] to CBT-E or INTER-E first. Participants’ inclusion criteria for studies 1–3 are age between 14 and 24 years, sufficient German language competences and written informed consent. Criteria for LOC [47] are fulfilled and youth included if they experience at least 3 episodes of LOC during the last 3 months accompanied by at least 3 out of 5 behavioral indicators and/or some degree of distress, absence of AN or BN. Inclusion criteria for youth participating in the HCG are healthy body weight (BMI 18.5–24.9), absence of any past or present ED and absence of any present mental disorder according to the diagnostic interview. Youth from the LOC group are excluded if they suffer from any current mental disorder preventing safe participation in the i-BEAT study or if there is an intake of weight affecting drugs, participation in an ED related psychotherapy or weight loss treatment. Females in pregnancy or lactation are excluded. Additional in- and exclusion criteria for study 2 are intact or corrected vision capacity and nausea in VR. Figure 3 illustrates the study sample.

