## Background

### Binge eating disorder (BED) and loss of control over eating (LOC)

Since the introduction of the fifth version of the Diagnostic and Statistical Manual of Mental Disorders (DSM-5 [1]) in 2013, BED, characterized by recurrent binge eating episodes associated with marked distress represents a separate entity in the section of feeding and eating disorders. BED is relatively common, associated with weight gain and detrimental consequences for mental and physical health [2]. Current research [3, 4] shows that BED variants are common during puberty and early adulthood, a period characterized by rapid biological changes, e.g. growth spurts, brain and secondary sex characteristics development, shifts in the accumulation of body fat. Puberty and early adulthood are furthermore accompanied by psychological challenges such as striving for autonomy and identity based on the acceptance of appearance and interpersonal competences [5]. This period at the age of c. 14 to 24 years has been named *youth* by the UN (www.unesco.org) and is critical for the onset of eating disorders (ED) [6]. A substantial group of youth experiences LOC, defined as loss of control eating over smaller food amounts which do not fulfil the criteria of an objective large food amount as required according to DSM-5, but with equivalent psychopathological relevance [7, 8]. The consequences of LOC in youth include weight gain, stress symptoms, substance use and low quality of life as well as increased suicide risks in female and male youth [9]. There is a consensus to apply age adapted criteria to capture the presentation of youthful BED variants and LOC (the two of them thereafter summarized as LOC). Existing research applies various frequency and duration criteria, from at least one LOC episode during the prior month to once a week during the previous 3 months [4, 10]. Up to now, most of the research in LOC relies on female participants, even though males are more often affected with BED and LOC than in other EDs [11].

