### Diagnostic assessment

Body weight and height are self-reported in study 1 and measured upon arrival for study 2 in light clothing to compute BMI (kg/m^2^). The diagnostic interview according to DSM-5, "Diagnostisches Interview bei Psychischen Störungen" (DIPS; [52]) is applied to identify mental disorders and LOC criteria, which are further confirmed via the Eating Disorder Examination Questionnaire (EDE-Q, German version; [53]). Frequency and severity of LOC or binge eating episodes are measured using the self-constructed weekly binge eating questionnaire (WBQ; [50, 54]). Measures and assessment time points during the i-BEAT study are presented in Fig. 2. In study 3, besides pre to post and follow-up measurements, the treatment process is assessed by weekly online questionnaires provided via the platform encompassing the primary outcomes frequency and severity of weekly LOC episodes, weekly interpersonal emotion regulation problems/ RS as well as attrition, adherence, dropouts, acceptance and feasibility.

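### The control group's single BMI band for ages 14 to 24 does not mean the same weight status at every age, and the Study 3 BMI-stability hypothesis makes no allowance for growth

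*Protocol article*

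**What the plan says.** All three studies admit participants with "age between 14 and 24 years" (Participants). The same section defines a healthy control's weight as "healthy body weight (BMI 18.5–24.9" kg/m²), one band for every age and both sexes.

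Diagnostic assessment computes BMI in kg/m². The article mentions no percentile, standard deviation score or growth reference.

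For Study 3, one hypothesis is that "BMI remains stable during active treatment and follow-up" (Study aims and hypotheses). Study design gives the time frame: "each of the two 6-weeks CBT-E or INTER-E modules", a 3-week pause between them, and follow-ups at 6 and 12 months. Every participant is due to receive both modules.

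The Background calls the period "a period characterized by rapid biological changes, e.g. growth spurts, brain and secondary sex characteristics development, shifts in the accumulation of body fat". It also says "There is a consensus to apply age adapted criteria to capture the presentation of youthful BED variants and LOC". Age adaptation is thus accepted for the eating-disorder criteria, but none is stated for weight status.

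**The concern.** In someone still growing, BMI in kg/m² depends on age and sex as well as on relative weight. Two things follow.

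- **Control selection.** A fixed floor of 18.5 and ceiling of 24.9 sit at different points of the BMI distribution at 14 and at 24. Young controls who pass are the heavier ones for their age; older controls who pass are, if anything, the lighter ones. The controls' relative weight then varies with age because of the entry rule.
- **BMI stability in Study 3.** After the wait there is no untreated group, so the hypothesis is judged on change within participants. Growth over more than a year can then look like weight gain, or hide a fall in relative weight.

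**Working it through.** The article gives no BMI mean, SD, growth rate or age mix, and no figure of its own to reproduce here. The means, SDs, growth rates and growing shares below are assumptions chosen to show direction and rough size.

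**1. Who passes the control band**

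Inputs: limits 18.5 and 24.9 (Participants). Assumed: BMI normal within an age group, SD 3; mean 19 or 20 for the youngest, 23 for the oldest.

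Share below = Φ((18.5 − mean)/3). Share above = 1 − Φ((24.9 − mean)/3).

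| Assumed mean | Below 18.5 | Above 24.9 | Total excluded |
|---|---|---|---|
| 19 | Φ(−0.167) = 43% | 1 − Φ(1.967) = 2% | 46% |
| 20 | Φ(−0.500) = 31% | 1 − Φ(1.633) = 5% | 36% |
| 23 | Φ(−1.500) = 7% | 1 − Φ(0.633) = 26% | 33% |

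(Unrounded, the first row is 43.4% + 2.5% = 45.8%.)

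Both limits must be counted. The lower one alone gives 31% to 43% against 7%. With both, the gap between youngest and oldest is 3 points (36% against 33%) to 13 points (46% against 33%).

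**2. Relative weight of those who pass**

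With a = (18.5 − mean)/3 and b = (24.9 − mean)/3, the mean position of those kept, in SDs from their own age group's mean, is (φ(a) − φ(b)) / (Φ(b) − Φ(a)).

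- Mean 19: (0.393 − 0.058)/0.542 = +0.62 SD
- Mean 20: (0.352 − 0.105)/0.640 = +0.39 SD
- Mean 23: (0.130 − 0.326)/0.670 = −0.29 SD

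The youngest controls kept are heavier than their age group and the oldest lighter. Matching on age does not remove this.

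**3. Growth over the Study 3 time frame**

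Inputs: 6 + 3 + 6 = 15 weeks from the start of module 1 to the end of module 2, then 12 months (Study design). The 4-week wait precedes treatment and is left out. Time: 15 × 7/365.25 = 0.287 years, and 1.287 years with follow-up. Drift = growth rate × time.

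| Assumed growth, kg/m² per year | End of module 2 | 12-month follow-up |
|---|---|---|
| 0.2 | 0.06 | 0.26 |
| 0.4 | 0.11 | 0.51 |
| 0.6 | 0.17 | 0.77 |

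These figures apply to participants still growing. The sample mean shifts by the drift times their share: 0.51 becomes 0.26 if half are growing and 0.13 if a quarter are.

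**4. What that does to a test of no change**

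Inputs: 120 randomised (Sample size) and 18% dropout, the upper end in Data analysis, so 120 × 0.82 = 98 completers. Assumed: growth 0.4 a year; SD of individual BMI change 1.0, 1.5 or 2.0. Probability that a two-sided 5% test finds an increase with no treatment effect = Φ(shift × √98 / SD − 1.96).

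- Half growing: 72%, 40%, 25%
- A quarter growing: 25%, 13%, 9%

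**The case against.** The strongest reply concerns scope.

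- **Study 2 matches controls on age and gender** (Study design). This stands for age balance, but matching equalises age, not relative weight.
- **Study 3 randomises only youth with LOC**, so the control band does not touch it. Correct.
- **The analysis scale may be set elsewhere.** The article is condensed, a Tanner questionnaire is listed, and kg/m² is the starting point for any standardised score. This limits the second half of the point: the hypothesis is stated without standardisation, but an analysis plan could supply it. The eligibility band is a stated rule that an analysis plan would not change.
- **BMI is a secondary outcome, and upward drift works against the stability hypothesis.** Both true. The risk is a false impression of weight gain or a masked benefit, not a false success.

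Stronger readings are tempting but not supported. A reader might infer that the control group will be markedly older than the LOC group; that comes from counting only the lower limit. A reader might infer bias in the comparison of CBT-E first with INTER-E first; growth is expected to fall equally on both orders. A reader might infer that the Study 1 association between rejection sensitivity and BMI is confounded by age. That needs rejection sensitivity to vary with age and age to be left unadjusted; the article states neither and plans covariates without naming them.

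**Conclusion.** The point holds in two limited parts.

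First, the control band is a stated rule at odds with the article's own account of these ages. Its main effect is on the relative weight of the controls kept. The effect on age mix is small to moderate, about 3 to 13 percentage points of extra exclusion in the youngest. Both results assume that mean BMI rises with age and use illustrative means and an SD of 3.

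Second, as worded, the Study 3 stability hypothesis cannot separate growth from weight change. The problem lies mainly at 6 and 12 months; over the 15 weeks of modules and pause the drift is at most 0.17 kg/m² under the growth rates assumed. By 12 months it is 0.26 to 0.77 in those still growing, diluted by an unknown share who have stopped.

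The change is worth making, but it does not threaten the randomised comparison and alters no sample-size figure.

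**What to change.** - **Control eligibility.** For controls under 18, define healthy weight by age- and sex-specific BMI percentiles from a named reference. Keep the present band for adults.
- **BMI stability in Study 3.** For participants who are minors at baseline, analyse age- and sex-standardised BMI, using the same reference throughout follow-up, including for those who turn 18. Use raw BMI for adults. Report raw BMI for everyone as a supplement.
- **Study 1.** At most, state that age and sex are among the planned covariates when BMI is the outcome.

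The cost is a short eligibility amendment and a few lines of analysis text. Standardisation needs only age, sex, height and weight, which the trial needs anyway. The downsides are that a reference must be chosen and named, and that minors and adults are reported on different scales.

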Hypotheses concerning (1) primary and (2) secondary outcomes in study 2:Exposure to the exclusion condition of the VR Cyberball task leads to greater social threat-related effects during and after the exclusion (lower HRV; increased negative/reduced positive affect, impairment of basic needs) and to a delayed recovery in youth with LOC compared to the HCG. Exposure to the exclusion condition of the VR Cyberball task leads to greater social threat-related effects during and after the exclusion (lower HRV; increased negative/reduced positive affect, impairment of basic needs) and to a delayed recovery in youth with LOC compared to the HCG.Exposure to the exclusion condition leads to higher values of body dissatisfaction and of urge to engage in disinhibited eating after the task and during recovery in youth with LOC compared to HCG.RS interpretation bias (underestimation of ball tosses while included, misinterpretation as being excluded during inclusion condition, negative evaluation of ambiguous social scenarios) is more pronounced in youth with LOC than in the HCG.Exposure to the exclusion condition leads to stronger pupillary dilation response, stronger hyperscanning (eye gaze), more closed hand posture, stronger aversion of social gaze (measured as gaze dwell time) in youth with LOC compared to the HCG.Youth with LOC show lower motor inhibition capacities indicated by longer SSRTs than the HCG during the gSST.The motor inhibition capacity group difference is especially apparent in the food stimuli condition of the gSST in the LOC group compared to the HCG.

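### Study 2 compares LOC youths who may have comorbid mental disorders with controls who may have none, so its differences cannot be attributed to LOC alone

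*Protocol article*

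**What the plan says.** All references are to the protocol article.

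- **Participants, controls:** the healthy control group (HCG) must show "absence of any past or present ED and absence of any present mental disorder according to the diagnostic interview".
- **Participants, LOC group:** the LOC definition requires episodes "accompanied by at least 3 out of 5 behavioral indicators and/or some degree of distress, absence of AN or BN". Beyond that, "Youth from the LOC group are excluded if they suffer from any current mental disorder preventing safe participation in the i-BEAT study". Other exclusions concern weight-affecting drugs, eating-disorder psychotherapy, weight-loss treatment, pregnancy and lactation. None of these limits depression or anxiety disorders.
- **Study design:** in study 2, "primary and secondary outcomes are compared between youth with LOC and age and gender matched HCG youth". No other matching variable is named.
- **Study aims and hypotheses, study 2:** the prediction is that being excluded "leads to greater social threat-related effects during and after the exclusion (lower HRV; increased negative/reduced positive affect, impairment of basic needs"). Slower recovery than in controls is also predicted for the LOC group. Further study 2 hypotheses concern interpretation bias, gaze and motor inhibition.
- **Data analysis:** an ANCOVA with moderators is planned for study 2. No covariates are listed and comorbid disorder is not mentioned.
- **Note to Fig. 2:** the full diagnostic interview (DIPS) is done before anyone enters study 2, so comorbidity will be known for its participants.
- **Abstract, Discussion:** the findings are expected to specify the role of interpersonal emotion regulation problems and rejection sensitivity in LOC.

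**The concern.** Take two youths with the same current social anxiety disorder, mild enough for safe participation, one with LOC and one without. The first can enter the LOC group. The second cannot enter the control group. The groups therefore differ by design in two respects, LOC and permitted comorbidity, and age and gender matching removes neither.

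Several study 2 outcomes (affect, need threat, HRV, social gaze, reading of ambiguous social scenes) are ones on which anxious or depressed youths could plausibly differ from healthy youths whether or not they have LOC. Where comorbidity worsens these outcomes, the bias runs in the hypothesised direction. A positive result would then not separate a stronger reaction in LOC youths from a stronger reaction in youths with a current disorder, although the article aims at a statement about LOC.

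**Working it through.** **1. The plan's own figure.** Inputs from Sample size: d = 0.8, power 0.8, alpha 0.05, about 13% dropout, N = 60. Assumed: two-sided test and equal groups. The two-sample t-test needs 25.5, so 26 per group and 52 in total; 52 / (1 − 0.13) = 59.8, so 60. The stated N reproduces, and the concern is not about sample size. Below, 26 completers per group are used.

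**2. Can a covariate repair it?** The rules side by side:

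| | Current non-eating mental disorder |
|---|---|
| HCG | none allowed |
| LOC | allowed unless it prevents safe participation |

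No control can have a diagnosis. If diagnosis entered the ANCOVA, its effect would be estimated within the LOC group alone and then extrapolated. Symptom scores could adjust in part only. The imbalance comes from eligibility, not from an unnamed covariate.

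**3. Size if LOC has no effect.** The documents give neither input, so both are assumptions: a share q of the LOC group has a disorder, and the disorder shifts the outcome (or, for a reactivity outcome, the reaction) by δ SD.

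- Spurious difference = q × δ.
- Extra variance in the LOC group = q(1 − q)δ².
- Pooled SD = √[(1 + 1 + q(1 − q)δ²) / 2].
- Standardised difference = qδ / pooled SD; rejection from the noncentral t at 26 per group, two-sided 5%.

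Example, q = 0.6 and δ = 0.8: 0.6 × 0.8 = 0.48; extra variance 0.24 × 0.64 = 0.154; pooled SD √(2.154 / 2) = 1.038; standardised 0.48 / 1.038 = 0.463; rejection 37.3%.

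| q | δ | q × δ | Share of planned 0.8 | Rejection |
|---|---|---|---|---|
| 0.20 | 0.3 | 0.06 | 7.5% | 5.5% |
| 0.30 | 0.5 | 0.15 | 19% | 8.2% |
| 0.45 | 0.8 | 0.36 | 45% | 23.2% |
| 0.60 | 0.8 | 0.48 | 60% | 37.3% |

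**4. Level and reactivity.** If comorbidity only moves a youth's general level of mood or HRV, that shift cancels from a change-from-baseline contrast. There δ counts only the part by which comorbidity alters the reaction or the recovery. For outcomes compared as levels, such as stop-signal reaction time, the whole shift counts.

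**5. Precision of a comorbidity-free contrast.** At q = 0.45, about 0.55 × 26 = 14 LOC completers remain. The 95% half-width in SD units is t × √(1/n₁ + 1/n₂):

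- 14 vs 26: 2.024 × 0.331 = 0.67
- 26 vs 26: 2.009 × 0.277 = 0.56

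**The case against.** **The comparator is declared.** The article calls the controls healthy throughout, and its hypotheses are worded as LOC versus HCG. A clinical group with its usual comorbidity against healthy controls is a recognised and generalisable contrast. This stands: the design is legitimate and recruitment need not change. What it does not license is a conclusion about LOC as such.

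**Comorbid affect may belong to the mechanism.** The Background places negative affect on the pathway to LOC. Dropping comorbid youths could remove part of the process and leave an atypical subgroup. This also stands. It is why the restricted contrast belongs beside the main one and should not decide attribution. A rule that accepts a LOC effect only when the two estimates are similar would need a definition of similar that 14 versus 26 participants could not support.

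**It is a matter for the analysis plan.** Choice of covariates is. The lack of overlap in diagnosis is fixed by the eligibility criteria, and no covariate choice removes it.

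**Stronger readings.** A reader might infer that LOC youths may have any disorder compatible with safety; AN and BN are barred. A reader might infer that every study 2 contrast is biased; a stable level difference does not bias a reactivity contrast. A reader might take the upper rejection rates as expected; they follow from assumed inputs, and at the low end the rate is barely above 5%.

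**Conclusion.** The concern holds as a limit on attribution. Under the written criteria, a study 2 difference between LOC youths and controls may partly reflect comorbid disorder, for outcomes compared as levels and for reactivity outcomes where comorbidity changes the response to exclusion. With assumed comorbidity of 20–60% and disorder effects of 0.3–0.8 SD, the spurious difference is about 0.06–0.48 SD and the rejection rate about 6–37% if LOC has no effect. These figures rest on 26 completers per group, a two-sided 5% test and equal allocation. The documents do not show where in that range the trial lies, and they do not support saying that a positive result would be spurious.

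**What to change.** Keep recruitment as it is.

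1. Pre-specify for study 2 a sensitivity analysis comparing LOC participants without a current non-eating mental disorder on the DIPS with the HCG. Do the same for App participants who have a DIPS; those who take part only in the App study may have none.
2. Report that estimate with its confidence interval beside the main contrast. Do not use it as a pass/fail rule for attribution.
3. Word the main conclusion as LOC youth with their usual comorbidity versus healthy youth, and claim no effect specific to LOC from the main contrast alone.

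The cost is one extra analysis of interview data already collected before study 2. The downside is an imprecise estimate, which may also exclude part of the mechanism, so it informs the reading of the main result without settling it.
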